### 2.8. Statistical Analyses

Statistical analyses will be performed at both national and cross-national levels. Data will be analyzed using intention-to-treat principles [119] and adjusted for cluster effect [62]. Baseline characteristics will be preliminarily compared to check equivalence between study groups using analysis of variance (ANOVA) and *χ*^2^ tests. To answer primary and secondary research questions, differences in primary and secondary outcomes between the study arms from T0 through T1 and T2 will be tested using linear mixed effect models. These analyses will be based on individual participant-level data, allowing for clustering between AYCs within the same school or geographical area [62,120]. Models will include the fixed effects of study arm, country and delivery approach, time and their interaction effects. The cluster will be considered as a random effect. Models will be adjusted for characteristics that are unbalanced between study arms and significantly associated with the outcome measures. In case of violations of assumptions underlying planned analyses (e.g., equal variance and normal distribution of residuals) appropriate mathematical transformations of raw scores (e.g., logarithmic scale) or robust estimation methods will be applied [121]. Interpretation of results will be based on both statistical significance (*p* < 0.05, two-tailed) and measures of effect size [122]. We will also summarize post-intervention self-assessment and process evaluation measures. Analysis of qualitative data in national languages (for control variables likes and dislikes about caring and for intervention acceptability) will be performed using content analysis [123].

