## 3. COVID-19-Related Amendments to Study Protocol Methods

The COVID-19 pandemic has introduced important challenges to the continuation of this study. To avoid costly trial closures, deviations from the original study protocol were deemed unavoidable by the research project team and amendments were made to the originally planned methodology. To comply with the restrictions and precautionary measures introduced at national levels, the study has been virtualized on April 2020, including remote enrollment, screening, consent and data collection, and a fully online delivery of the ME-WE intervention and of training and supervision of facilitators [126,127]. COVID-19-related amendments to the study protocol methods are described in detail in the following subsections. If not specified below, the original study protocol as described in Section 2 will be followed.

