### 3.5. Sample Size Calculation Amendments

The minimum required sample size was revised for Sweden and Switzerland, since randomization in these countries will occur at the individual participant level. A minimum group size of 24 AYCs was established based on power analyses with a medium effect size, a power of 80% and an α-error probability of 5%. Compensating for attrition (20%), a minimum total sample size of 58 AYCs (29 AYCs in the intervention and 29 AYCs in the waitlist group) will be required in Sweden and Switzerland.

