### 3.6. Statistical Analyses Amendments

For countries that turned to an individual-based RCT (i.e., Sweden and Switzerland), statistical analyses will be performed at the individual participant-level, with no cluster-based adjustment. Statistical analyses at the cross-national level will be performed separately for countries conducting cluster RCTs (i.e., Italy, Slovenia, the Netherlands and United Kingdom) and countries conducting individual-based RCTs (i.e., Sweden and Switzerland). For individual based RCTs, differences in primary and secondary outcomes between the study arms from T0 through T1 and T2 will be tested using mixed ANOVA. Models will include the effects of study arm, country, time and their interaction effects. In case of violations of assumptions underlying planned analyses, appropriate data transformations or robust estimation methods will be applied [121]. Analysis of qualitative data collected using newly added COVID-19-related open-ended questions in national languages would be performed using content analysis [123].

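### Mixed ANOVA for Sweden and Switzerland, as ordinarily run, drops participants with a missing wave and so works against the intention-to-treat principle; a likelihood-based mixed model would avoid this

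*Protocol article*

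**What the plan says.** Section 2.8 of the protocol article sets the general principle: "Data will be analyzed using intention-to-treat principles". It names the method for all countries as first planned: arm differences "from T0 through T1 and T2 will be tested using linear mixed effect models". The only random effect it names is the cluster.

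Section 3 introduces the COVID-19 amendments with a carry-over rule: "If not specified below, the original study protocol as described in Section 2 will be followed". Nothing in section 3 withdraws intention-to-treat.

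Section 3.6 then changes the method for Sweden and Switzerland, which now randomise individuals: "differences in primary and secondary outcomes between the study arms from T0 through T1 and T2 will be tested using mixed ANOVA". On content it adds "Models will include the effects of study arm, country, time and their interaction effects". It names no handling of a missing T1 or T2 assessment. The four cluster-randomised countries keep the linear mixed model.

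Loss is expected. Section 3.5 reads "Compensating for attrition (20%), a minimum total sample size of 58 AYCs", split 29 and 29. I take this as the figure for each country, since section 2.7 gives its totals country by country. The Discussion (section 5) states that the article details the statistical analysis plan.

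**The concern.** A mixed (split-plot) ANOVA treats time as a within-person factor and, as standard routines run it, requires a complete set of waves. A participant seen at T0 and T1 but not at T2 is removed entirely, including the T0 and T1 scores already collected. Under a promise to analyse by intention-to-treat, that is a stated method working against a stated principle.

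Two things are at stake. Observed T1 data are discarded in what are now the smallest planned national samples. And if those who leave differ from those who stay in a way already visible in their recorded scores, the comparison among completers can be biased where a likelihood analysis of all observed waves would correct for it. The move to individual randomisation explains removing the cluster adjustment. It does not by itself call for a method that needs complete data.

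**Working it through.** **1. The plan's own figure.** Inputs: f = 0.25 (section 2.7; section 3.5 says medium), power 80%, alpha 5%, two arms, three waves. The correlation between waves, ρ, is not given. For the arm-by-time interaction in a repeated-measures ANOVA with N participants and m waves, the noncentrality is λ = f²·N·m/(1−ρ), with 2 and 2(N−2) degrees of freedom.

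- With an assumed ρ = 0.1 and N = 48: λ = 0.0625 × 48 × 3 / 0.9 = 10.0, and power is 0.802. This reproduces 24 per group.
- Other values of ρ do not: ρ = 0 needs 54 in total, ρ = 0.2 needs 44, ρ = 0.5 needs 28.
- Attrition: 24 × 1.2 = 28.8, rounded up to 29 per arm, 58 in total, as stated.

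**2. Participants a complete-case mixed ANOVA would exclude at the planned 20%.**

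- Per country: 58 × 0.20 = 11.6, about 12, leaving 29 × 0.8 = 23.2 per arm.
- Sweden and Switzerland together: 116 × 0.20 = 23.2, about 23.
- Power with 23 per arm (ρ = 0.1): λ = 0.0625 × 46 × 3 / 0.9 = 9.58, power 0.78 against 0.80 at 48.

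**3. Precision at T1.** Suppose everyone is seen at T0 and T1 and losses occur before T2. With unit variance, the arm difference in T1−T0 change has standard error √[2 × 2(1−ρ)/n] for n per arm. At n = 29 and ρ = 0.5 this is √(2/29) = 0.263. Keeping only a fraction 1−d multiplies it by 1/√(1−d): 1/√0.80 = 1.12 at 20% loss and 1/√0.72 = 1.18 at 28%. The simulation below agrees: 0.158–0.314 for completers against 0.141–0.263 with all available data, about 10–20% larger. Loss of 28% enters only as an assumed upper setting.

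The gain at T2 is smaller, because those lost have no T2 score. In a run with 29 per arm, ρ = 0.5 and random drop-out of 24%, the standard deviation of the T2 contrast was 0.304 for completers and 0.293 by likelihood.

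**4. Possible bias (assumed mechanism).** Simulation of 3,000 trials per setting: no true effect, 29 or 58 per arm, equal correlations of 0.5 or 0.7, loss of 20% or 28% all between T1 and T2. Control loss was random. Intervention-arm drop-out log-odds rose by 0.5–1.0 per SD lower T1 score.

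| Contrast | Completers | All available waves |
|---|---|---|
| T1−T0, mean bias | +0.03 to +0.12 SD | at most 0.006 SD |
| T2−T0, mean bias | within 0.011 SD | not tabulated |

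The T2 result follows from the covariances. Selection on T1 shifts the T2−T0 change only through cov(T2−T0, T1) = ρ₁₂ − ρ₀₁, which is zero under equal correlations. For T1−T0 the corresponding term is 1 − ρ₀₁, which is not.

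A second run used a true effect of 0.50 SD, 29 per arm and steeper drop-out slopes of 0.75 and 1.5. The completer T1 effect was 0.59 and 0.67 SD. The completer T2 effect was 0.50 SD under equal correlations of 0.5. It was 0.54 and 0.56 SD when T1 and T2 correlated 0.7, T0 and T1 0.5, and T0 and T2 0.35. The likelihood estimate stayed at 0.50 SD throughout. With drop-out unrelated to outcome, both methods were unbiased.

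**The case against.** **The article does not state a completers-only analysis.** A reader might infer that section 3.6 fixes one. It names a test and is silent on missing waves. Mixed ANOVA can be run on imputed data, and the same terms can be fitted by likelihood; such detail may sit in a fuller document. This stands as a limit on the claim. It does not remove the point: the named method in its ordinary form conflicts with a principle in force, and the article presents itself as detailing the analysis plan.

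**It is not enough to delete the cluster term.** A reader might think the section 2.8 model could serve once that term is removed. That section names only a cluster random effect, with no participant effect or covariance over waves. Removing the cluster would leave within-person correlation unmodelled, whereas mixed ANOVA accounts for it. The switch therefore had a rationale, and the replacement must state the within-person structure.

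**Sphericity.** The unequal spacing of the waves might suggest a further fault. Section 3.6 already allows transformations or robust estimation when assumptions fail, so this is not pursued. That clause does not restore excluded participants.

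**The 28% loss in section 4.** It is tempting to apply it here. It comes from 22 Italian participants, in a cluster-randomised country, with data from October 2019 to March 2020, before the trial was virtualised in April 2020. It does not establish the loss to expect in Sweden or Switzerland.

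**The bias scenario is selective.** This stands. With half the loss before T1 (assumed to depend on T0 in the intervention arm), completer bias at T1 was at most 0.012 SD, and at T2 it was −0.01 to −0.06 SD. In the main scenario a true null at T1 was rejected 5–8% of the time. The biases are mostly small beside standard errors of 0.16–0.31.

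**Lost precision is largely budgeted.** The inflation from 24 to 29 leaves about 23 per arm, so power against the plan's own target barely moves. What is lost is information collected and not used.

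**Different analysis populations across country sets.** This adds little: section 3.6 analyses the two sets separately and does not pool them.

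**Conclusion.** The point holds as a tension between a named method and a stated principle. As ordinarily run, mixed ANOVA would exclude about 12 of 58 participants per country (23 of 116 pooled) at the planned attrition, while intention-to-treat still governs Sweden and Switzerland. These counts take the 20% to mean missing at least one wave.

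The dependable consequence is a standard error for the T1 contrast about 12% larger at 20% loss, within the simulated range of about 10–20%. Bias is a possibility, not a finding: about 0.03–0.12 SD at T1 if intervention-arm drop-out after T1 depends on the T1 score, little or none at T2 under equal correlations, and none if loss is unrelated to outcome. The documents do not tell us the drop-out mechanism or the correlations between waves.

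This should be fixed before analysis, but it does not undermine the design, and it should not be read as showing that the results for these two countries will be biased.

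**What to change.** In section 3.6, replace mixed ANOVA with a likelihood-based linear mixed model for Sweden and Switzerland that has:

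- study arm, country, time and their interactions as fixed effects, as section 3.6 already lists;
- every randomised participant with at least one observed wave, and all their available T0, T1 and T2 scores;
- within-person correlation over the three waves modelled explicitly, by an unstructured covariance or a participant random effect, which must be written in because section 2.8 names neither;
- no school or area cluster term.

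Report the completers-only result as a sensitivity analysis.

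The cost is about one sentence of text. No new data, visits or participants are needed, and section 4 describes the trial as still ongoing, so the change can be made before the data are analysed.

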### 2.5. Outcome Measures

Demographic (gender, age, country of birth, nationality, migration background, place of living, living conditions and family composition) and caregiving information (number and age of people cared for, type of relationship with the care recipient, nature of the illness or health condition of the care recipient and time since caregiving started) will be collected at baseline (T0). Primary and secondary outcomes and control variables will be collected at baseline (T0), post-intervention (T1) and 3 months post-intervention (T2). T0, T1 and T2 assessments in the ME-WE intervention group will be performed at the beginning of session 1, at the end of session 7 and at the beginning of session 8, respectively. Primary outcome variables will include psychological flexibility, mindfulness skills, resilience, subjective mental and physical health, general and caring-related quality of life, impact of caring and social support. Secondary outcome variables will be self-reported school/training/work experience, performance and attendance. The following variables will be used as control variables: caring activities, overall amount of caring, likes and dislikes of caring, formal support received and caring-related perceived social support. Both quantitative and qualitative data will be collected using a questionnaire available in both web-based and paper-and pencil versions. All selected standardized self-report measures were specifically developed and/or tested for use with adolescents. Measures not available in the local languages of participating countries have been translated after permission from the authors. The committee translation method was used [71]. Specifically, in non-English countries, two independent researchers fluent in English independently translated each measure from English into their local language, and then met to discuss eventual discrepancies and reach consensus on an integrated version. English questionnaires were used for participants in the United Kingdom. Ad-hoc developed items were formulated in English and then translated using the same procedure used for standardized tools. Participants in the intervention group will complete a post-intervention self-assessment tool at T1 and T2. Process evaluation outcomes will include feasibility, acceptability and fidelity indicators.

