#### 2.5.5. Process Evaluation Outcomes

A number of process evaluation outcomes will be monitored, following Linnan and Steckler [111]. Indicators of feasibility will include the proportion of eligible AYCs who will participate in the trial, the proportion of AYCs in the intervention group who will attend ≥70% of intervention sessions, and the proportion of AYCs who will be lost to follow-up. These feasibility indicators will be assessed using attendance lists (for the intervention group) and completion of assessment questionnaires (for the control group). To assess intervention acceptability, 5 open-ended questions included in the post-intervention self-assessment [110] will ask AYCs for their perceptions about the support they received from the intervention, what changed for them and for their caring role because of participating in the intervention and what they did not like about the intervention. For fidelity, a semistructured questionnaire will be completed by cofacilitators following each intervention session to evaluate whether the ME-WE intervention was delivered as planned.

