## 4. Trial Status

The recruitment of participants started in May 2019. Randomization began in September 2019, and the first baseline assessment was completed on 24 October 2019. Before COVID-19-related amendments (April 2020), a total of 98 AYCs was recruited. The trial is currently ongoing. Preliminary data available from Italy (*n* = 22, October 2019–March 2020) indicated feasibility of the ME-WE trial and acceptability of the ME-WE intervention. The proportion of eligible AYCs (screened between May and September 2019) who participated in the trial was 84%. Seventy-three percent of AYCs in the intervention group attended at least 70% of intervention sessions. Twenty-eight percent of all participants were lost to follow-up. Responses of AYCs in the intervention group to the post intervention self-assessment indicated that participants had a clearer vision of their thoughts, took better care of themselves and were generally satisfied with and enjoyed the intervention.

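### Sweden and Switzerland move to mixed ANOVA, which in standard form drops anyone missing a wave, in tension with intention-to-treat; in all countries intervention-arm assessments sit inside treatment sessions

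*Protocol article*

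**What the plan says.** Section 2.8 sets the principle: "Data will be analyzed using intention-to-treat principles". It also names the method: differences between arms over the three waves "will be tested using linear mixed effect models", with cluster as the random effect.

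Section 3 keeps Section 2 in force where the amendments are silent: "If not specified below, the original study protocol as described in Section 2 will be followed". Section 3.6 is not silent on the method. For the two countries that now randomise individuals, Sweden and Switzerland, differences "between the study arms from T0 through T1 and T2 will be tested using mixed ANOVA", with arm, country, time and their interactions in the model. It says nothing that withdraws intention-to-treat, so that promise still covers these two countries.

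On measurement, Section 2.5 states that the intervention-arm assessments "will be performed at the beginning of session 1, at the end of session 7 and at the beginning of session 8". Section 2.4 places control assessments at three meetings arranged for data collection. Section 3.4 moves the questionnaires to the web but does not detach them from the sessions.

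On retention, Section 2.5.5 lists loss to follow-up among the feasibility indicators and says that these are "assessed using attendance lists (for the intervention group) and completion of assessment questionnaires (for the control group".

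Section 4 gives preliminary Italian figures (n = 22, October 2019 to March 2020): "Twenty-eight percent of all participants were lost to follow-up".

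**The concern.** Mixed (split-plot) ANOVA in its usual form needs a complete set of T0, T1 and T2 scores, and a participant missing one of them leaves the analysis. Unless missing waves are filled in, the analysed set is the completers, which is not the set that intention-to-treat promises. Ending cluster randomisation did not require this change. A linear mixed model with a participant-level term instead of a cluster term suits individual randomisation and keeps partial records.

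The second issue is separate and applies in all six countries. If the questionnaire is completed at a treatment session, whether an intervention participant is measured depends on whether he or she is still attending treatment. Control participants also attend meetings to be measured, but attending those meetings is not exposure to treatment. Loss of data is therefore linked to adherence in one arm only.

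At stake are precision in two small national samples, the credibility of the intention-to-treat label, and a retention comparison that does not count the same thing in both arms.

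**Working it through.** **Inputs.** Sections 2.7 and 3.5: f = 0.25, power 80%, α 5%, 24 per group, 20% for attrition, 58 in total (29 per arm) in each of Sweden and Switzerland. Section 2.8: two-tailed test. Section 4: 28% lost, 22 Italian participants before the amendments.

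**The plan's own figure.** 24 × 1.2 = 28.8, rounded up to 29 per arm, 58 in total. This reproduces the stated number. The number needed after attrition is 2 × 24 = 48.

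**Complete cases under mixed ANOVA**, reading the loss as the share of participants missing at least one wave:

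- 20% loss: 58 × 0.80 = 46.4, about 46, or 23 per arm.
- 28% loss: 58 × 0.72 = 41.8, about 42, or 21 per arm.

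Both are below 48. The 20% case falls short because 24 was multiplied by 1.2. Dividing by 0.8 gives 30 per arm and 60 in total, and 60 × 0.80 = 48.

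**What this does to power.** The article does not state the correlation between waves, so one must be assumed. With a noncentral F for the arm-by-time interaction (2 groups, m = 3 waves, sphericity, noncentrality f² × N × m / (1 − ρ)), a total of 48 is returned when ρ is about 0.1. With ρ = 0.1 held:

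| Participants with complete data | Power |
|---|---|
| 58 | 87.6% |
| 48 | 80.2% |
| 46 | 78.3% |
| 42 | 74.1% |

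The result is sensitive to ρ. At ρ = 0.5 the same formula needs only 28 in total, and power at 42 is 94.6%. The power loss is thus modest at the planned attrition and depends on an unstated input. A mixed model would recover part of it, from participants who give some but not all waves. The 87.6% is a ceiling that needs every wave from everyone.

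**The measurement texts side by side.** Section 2.5 fixes the intervention-arm occasions as sessions. Section 2.4 fixes the control occasions as data-collection meetings. Section 3.4 changes the medium only. No section describes an assessment for someone who misses session 1, 7 or 8, and none rules one out. For loss to follow-up, Section 2.5.5 uses attendance in one arm and questionnaire completion in the other. An intervention participant who answers the web form without attending could count as lost, while a control who does the same would count as retained.

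**The case against.** Several points on the other side are fair.

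- Section 3.6 names mixed ANOVA but does not say complete cases only. ANOVA after imputation would be compatible with intention-to-treat, and handling of missing data is often left to a full analysis plan. This stands in part: the text supports tension, not outright contradiction. Against it, Section 5 says the article sets out the statistical analysis plan, and the point concerns a named method replacing a better one, not a missing detail.
- A reader might infer that the analysed intervention arm becomes the attenders, set against controls who merely answered a questionnaire. The document does not support that. Control assessments are tied to meetings too (Section 2.4), and nowhere is it said that absentees go unmeasured. Section 5 lists reminders among the retention measures, and the form is now online.
- A reader might also infer a bias towards benefit, for example 0.28 times an assumed gap of 0.2 to 0.5 SD between leavers and stayers, or 0.06 to 0.14 SD. That does not hold up. The 28% covers both arms of a small Italian sample before the amendments. The sum assumes no selection in controls. It is also a difference in level, whereas the planned test concerns change over time, so a gap already present at baseline would cancel. Changing the model alone would not remove such a bias if dropout depends on unobserved response.
- Section 2.5.5 governs feasibility indicators, one of which (attendance at 70% or more of sessions) can only come from attendance lists. It does not define the efficacy analysis set. This stands; the defect there is confined to comparing retention.
- Seven weekly sessions span six weeks, against seven weeks to T1 for controls. This is too small to carry weight.

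**Conclusion.** The point holds in a limited form and should be fixed.

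For Sweden and Switzerland, the amended method is in tension with an intention-to-treat promise that remains in force, and it wastes partial data. The analysed number per country would be about 46 of 58 at the planned attrition, against 48 required, and about 42 if loss reached 28%. This rests on two assumptions: that mixed ANOVA is run in its standard complete-case form, and that the attrition figure is the share missing any wave. The 28% is indicative only; the 46 does not depend on it.

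In all countries, intervention-arm measurement as written depends on attending treatment sessions. That creates a route to bias, but its size and direction depend on who stops attending and cannot be settled from the document. Retention rates taken from attendance in one arm and questionnaires in the other are not comparable.

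**What to change.** 1. In Section 3.6, replace mixed ANOVA for Sweden and Switzerland by a linear mixed model on all available waves, with arm, country, time and their interactions as fixed effects, no cluster term, and a participant-level random effect or a within-person covariance. The within-person term must be written in, because Section 2.8 names only cluster as random.
2. In Sections 2.5 and 3.4, send the existing web questionnaire at T1 and T2 to every randomised participant in both arms, whether or not they attended, and where feasible collect T0 before session 1.
3. In Section 2.5.5, define loss to follow-up in both arms as no completed questionnaire, and keep attendance lists for the attendance indicator.

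The first and third are changes of wording. The second needs a few more reminders and a small change to assessment logistics in a trial already under way, with 98 participants recruited before April 2020. The first keeps partial records but cannot replace data never collected, and it still assumes that missingness is explained by observed data, so the second is worth doing with it.
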